### Data collection and management

#### Plans for assessment and collection of outcomes {18a}

All examination forms will be printed and filled out by the assessor during each examination, with uniform training provided to the assessor to ensure greater consistency. The questionnaires will also be printed and completed by the patients. Data from the wearable device will be extracted from the app's backend by a statistician who is not involved in the trial intervention. Two data administrators will enter the data into anonymized tables that set up logical errors, such as mandatory fields and limits responses that violate common sense, and the data in the tables will subsequently be utilized for statistical analysis.

#### Plans to promote participant retention and complete follow-up {18b}

Patients will be given thorough information about the trial, including its design and needs, during the recruitment process. They will also be reminded of how crucial it is to finish the trial. Patients are free to stop participating in the study at any time and are not required to provide a reason. A quality form will be utilized to gauge the patient’s development, and patients will be reminded to assist with the researcher’s scale assessment at several points during the survey. Participants who have stopped or departed from intervention regimens will have their outcome information collected.

#### Data management {19}

All experimental procedures and data will be documented in a case report form by the outcome assessors. Each participant will be assigned a unique identification code to safeguard patient privacy. Access to the case report forms will be restricted solely to the outcome assessors and the corresponding author. All data entries will undergo a double-checking process by two independent assessors. Once entered and verified, the data within the case report forms will be rendered unmodifiable.

### Statistical analysis

#### Statistical methods for primary and secondary outcomes {20a}

The criteria of the Consolidated Standards of Reporting Trials (CONSORT) shall be followed in the calculation and reporting of summary data [40]. We will evaluate the descriptive features and baseline outcome metrics and baseline comparability between groups. During trial and follow-up, a variety of reasons can lead to patient drop-out and loss, so intention-to-treat analysis (ITT) and per-protocol analysis (PP) are required for data. ITT analysis refers to the analysis of the data obtained after the elimination of all randomly assigned subjects in a minimum and reasonable method, while PP analysis refers to the analysis of only the data of the observation objects who have completed the whole experiment after randomization [41]. However, ITT analysis prevents bias due to the subjects’ violation of protocol, loss of follow-up, and generally makes differences between the two groups less detectable and conservative; PP analysis, on the other hand, usually exaggerates the differences between the two groups. In order to avoid overstating the efficacy, ITT analysis will be used as the main analysis set in this study.

We will use IBM SPSS, version 26.0.1 for all statistical analyses, with 2-tailed tests as appropriate, and 2-sided *P* < 0.05 considered to be statistically significant. Baseline data on categorical variables (e.g., sex, occupation, education level) will be used to compare statistical differences between the trial and control groups using chi-square tests. For continuous variables (e.g., age, BMI, pain intensity, duration of knee pain), a normality test will be first conducted. If all groups meet normality, mean ± standard deviation (SD) will be used for statistical description, and two independent sample *T* tests or Mann–Whitney *U* tests will be used for comparison between groups. Otherwise, the median (interquartile spacing) will be used for statistical description, and a nonparametric test will be used for comparison between groups. If the results of the trial meet the conditions of homogeneity of variance and spherical symmetry, the two-factor four-level repeated measurement analysis of variance (group*time) is used; otherwise, the mixed effects model is used. According to the recommendations of the International Conference on Osteoarthropathy [42], the minimum clinically important difference (MCID) could be achieved when the pain intensity (primary outcome index: VAS) between the two groups is changed by 18 mm based on 100 mm. A chi-square test will be used to infer the proportion of the number of patients meeting the MCID between the two groups. The measurement results of all outcome indicators will calculate the effect size, and the size of the effect size between the two groups will be compared according to Cohen’s criteria [38] to draw the appropriate conclusions.

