### Outcome measures {12}

After obtaining informed consent, a baseline assessment will be conducted. The details gathered include participants’age (acquired using the birthdate shown on their ID cards), gender, height, weight, BMI, education level, occupation, income source, hobbies, interests, marital status, smoking and alcohol use, medical history, knee pain duration, pain severity (current, worst, mildest), triggers, alleviating factors, and pain-avoiding behaviors. The primary and secondary outcomes will be evaluated before commencing the trial (baseline) and at 4-, 8- and 12-week post-intervention (shown in Table 2). We focus on changes in outcomes at 12 weeks after treatment.

**Table 2 Tab2:** Overview of the measurements and timing of measurements

Domain	Reporting methods	Questionnaire line	Base	4 weeks	8 weeks	12 weeks
Demographic characteristics	Self-reported	Purpose built	√	-	-	-
Pain intensity	Self-reported	VAS	√	√	√	√
Physical function	Self-reported	WOMAC	√	√	√	√
	Walking ability	TUG	√	√	√	√
Quality of life	Self-reported	SF-36	√	√	√	√
Self-efficacy	Self-reported	PSEQ	√	√	√	√
Mental health status	Self-reported	DASS21	√	√	√	√
Fear-avoidance in exercise	Self-reported	TSK	√	√	√	√
Pain catastrophic imagery	Self-reported	PCS	√	√	√	√
Exercise adherence	Self-reported	EARS	-	√	√	√
	Events	Movement completion rate	-	√	√	√
Adeverse events	Self-reported	-	-	√	√	√

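### Baseline data are spent on significance tests between randomised arms, while the stated group-by-time analysis uses baseline less efficiently than covariate adjustment would

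*Protocol article*

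**What the plan says.** All of the analysis text is in the protocol article, under statistical methods for primary and secondary outcomes ({20a}).

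- **Aim of the baseline comparison:** "We will evaluate the descriptive features and baseline outcome metrics and baseline comparability between groups".
- **Categorical variables:** sex, occupation and education level are given as examples, and these data "will be used to compare statistical differences between the trial and control groups using chi-square tests".
- **Continuous variables:** "For continuous variables (e.g., age, BMI, pain intensity, duration of knee pain), a normality test will be first conducted", after which t, Mann-Whitney or other nonparametric "tests will be used for comparison between groups". The two-sided 0.05 level is set for all analyses.
- **Outcome model:** if homogeneity of variance and sphericity hold, "the two-factor four-level repeated measurement analysis of variance (group*time) is used; otherwise, the mixed effects model is used". No covariate is named for either model.

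The outcome measures section ({12}) lists a long baseline set, including "gender, height, weight, BMI, education level, occupation, income source, hobbies, interests, marital status, smoking and alcohol use, medical history, knee pain duration". Its Table 2 shows that VAS, WOMAC, TUG, SF-36, PSEQ, DASS21, TSK and PCS are all taken at baseline and at 4, 8 and 12 weeks. On the time point of interest it says "We focus on changes in outcomes at 12 weeks after treatment".

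**The concern.** If the concealed 1:1 allocation works as described, every baseline null hypothesis is true by design, and a small P value carries no information about bias. The planned tests can mislead in two ways. They may produce a significant imbalance that means nothing. They may also produce a run of non-significant results that is read as proof of comparability, which a trial of this size cannot give.

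Meanwhile the most useful baseline measurement, the outcome's own starting value, enters the analysis only as one more response level. The difference in change from baseline then subtracts the whole baseline value, when the best linear use of it subtracts only the correlated part. At stake is precision on the primary comparison, from data that are already collected.

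**Working it through.** **Inputs.** From the sample size section ({14}): effect size 0.3, alpha 0.05, power 0.8, intraclass correlation 0.6, two groups measured four times, 64 patients, 25% dropout, 86 in total. From the design section ({8}): 1:1 allocation, hence 43 per arm randomised and 32 per arm after the planned dropout.

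**Plan's own figure.** Reading 0.3 as Cohen's f for the between-groups effect of a repeated measures ANOVA, the noncentrality is f²·N·m / (1 + (m−1)ρ). With N = 64, m = 4 and ρ = 0.6 this is 0.09 × 64 × 4 / 2.8 = 8.23, which gives power 0.806; N = 62 gives 0.793. So 64 reproduces, and 64 / 0.75 = 85.3 rounds up to 86. This shows that 0.6 serves as the correlation among the repeated measurements, so it can be used below.

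**Baseline tests: false alarms.** For k independent tests at 0.05, the chance of at least one significant result is 1 − 0.95^k.

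| Variables tested | k | Independent | Correlation 0.2 to 0.5 between tests |
|---|---|---|---|
| Named in {20a} (3 categorical, 4 continuous) | 7 | 30% | 29% to 23% |
| All baseline items in {12} | 21 | 66% | not computed |
| Those items plus 8 baseline outcome scores | 29 | 77% | 71% to 50% |

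The count of 29 is an upper reading. It treats height, weight and BMI as separate, hobbies and interests as separate, and current pain as distinct from baseline VAS. The correlated figures come from simulated equicorrelated normal test statistics.

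**Baseline tests: false reassurance.** For a two-sided t test with 43 per arm and a true imbalance of 0.3 SD, the noncentrality is 0.3 × √(43/2) = 1.39 on 84 degrees of freedom, and power is 0.28. A 0.3 SD difference would go unflagged about 72% of the time.

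**Precision of the 12-week contrast.** Assume equal SDs over time and correlation ρ between baseline and week 12. Express variance relative to a comparison of week-12 values alone.

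- Change from baseline, which is what the group-by-time contrast at week 12 estimates with complete data: 2(1 − ρ) = 2 × 0.4 = 0.80.
- Baseline as covariate: 1 − ρ² = 1 − 0.36 = 0.64.
- Ratio: 0.64 / 0.80 = 0.80, so 20% less variance. Standard error ratio: √0.80 = 0.894, about 10% lower.
- Sensitivity: 25% less variance at ρ = 0.5 (0.75 against 1.00) and 15% less at ρ = 0.7 (0.51 against 0.60).

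A simulation of 20,000 trials at ρ = 0.6, with the covariate slope estimated in each, gave standard error ratios of 0.902 with 64 patients and 0.895 with 86. The gain therefore survives the cost of the extra degree of freedom.

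**In patients and detectable difference.** The precision of 64 patients analysed by change is reached with 64 × 0.80 = 51.2, so 52, under adjustment. With 32 per arm, the difference detectable at 80% power (normal approximation) is (1.96 + 0.84) × √(2/32) × √variance = 0.70 × √variance: 0.63 SD for change and 0.56 SD with adjustment.

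**The case against.** Four objections deserve an answer.

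1. **No decision hangs on the baseline tests.** This stands. The protocol ties no exclusion, model choice or covariate to a baseline P value, so deleting the tests alone alters a table and no trial result. The remaining harm is a misleading sentence in the report.

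2. **A covariate list commonly sits in the statistical analysis plan, which is not shown.** This stands for additional covariates, and their absence from the article is no finding. It does not cover the baseline tests, which the article states outright. Nor does it cover the ANOVA, which is named with four levels over an outcome measured at baseline and three later visits.

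3. **An unadjusted analysis of a randomised trial is valid.** Correct. Its standard error already allows for chance imbalance. The point here is efficiency, not bias.

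4. **Baseline differences in the outcome are already handled.** Also correct. A reader might infer that chance differences in prognostic factors are left wholly uncorrected. For the outcome itself that is wrong, because the group-by-time contrast removes its baseline difference. A reader might also expect adjustment for Kellgren-Lawrence grade, BMI or pain duration to sharpen the estimate noticeably. The documents do not support that: a covariate that is constant over time largely cancels from a within-patient contrast unless it predicts change, and they give no figure for how well these factors do so.

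It would also go too far to say that a spurious imbalance is likely. That holds only if most of the full baseline set is tested, which {20a} does not say. For the seven named variables the chance is about 30%.

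**Conclusion.** The point holds as a modest improvement in method, not as a threat to validity. The baseline significance tests serve no inferential purpose, and neither a significant nor a non-significant result would mean what a reader would take from it. Separately, the 12-week group-by-time contrast has 25% more variance than a baseline-adjusted one at the protocol's correlation (0.80 / 0.64 = 1.25). Put the other way, adjustment saves 20% of the variance and about 10% of the standard error.

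The precision figures assume equal SDs over time, a baseline to week-12 correlation equal to the protocol's 0.6, and complete data. Over correlations of 0.5 to 0.7 the saving is 25% to 15%. The comparison concerns the 12-week contrast that the protocol emphasises. The figure of 64 reproduces for a different test, the overall between-groups effect, so this is not a finding that the stated sample size is wrong.

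**What to change.** In section {20a} of the protocol article:

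- Remove the between-arm tests of baseline variables. Present baseline data by arm with the descriptive statistics already planned and no P values.
- Analyse the 4-, 8- and 12-week values as the response, with group, time and their interaction, and with the outcome's own baseline value as a covariate: VAS for the primary outcome, and the matching score for each secondary outcome measured at baseline.
- Take baseline out of the response levels, so that the same value does not stand on both sides of the model.
- State that the covariates are fixed in advance and are not chosen by observed imbalance or P values.

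Further covariates such as Kellgren-Lawrence grade, BMI or knee pain duration are optional, and no gain in precision should be claimed for them.

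The cost is a change of analysis wording and one model degree of freedom. No new data, visits or patients are needed.

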**Methods and analysis:**

Patients diagnosed with knee osteoarthritis, who have not undergone knee surgery in the past year, will be recruited for a randomized controlled trial. The trial will include an intervention group and a control group. The intervention group will receive an mHealth app-based multicomponent exercise therapy, consisting of exercise therapy, patient education, and health coaching. Meanwhile, the control group will receive usual care, involving drug therapy and patient education. The primary outcome of the trial will be the measurement of pain intensity, assessed using a visual analog scale at baseline and at 4, 8, and 12 weeks of the post-intervention. To analyze the data, a two-factor, four-level repeated measures ANOVA will be used if the assumptions of homogeneity of variance and sphericity are met. If not, a mixed effects model will be employed.

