### Participant timeline {13}

This study will commence with the eligibility screening of prospective participants. Those meeting the eligibility criteria will be enrolled in the study and briefed on the procedures entailed. Participants deemed eligible and willing will be required to provide written informed consent (accessible in Additional File 2) prior to enrollment. We will assess their outcomes at the outset (W0), following 4 weeks of treatment (W5), 8 weeks of treatment (W9), and 12 weeks of treatment (W13). The schematic diagram illustrating the participant timeline is depicted in Fig. 1.

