### The explanation for the choice of comparators {6b}

Patients in the control group will receive usual care rehabilitation treatment, with app-based patient education (10 min per day, 1 day per week, for 12 weeks) and topical use of NSAIDs, diclofenac diethylamine latex (4 times a day, 7 days per week, for 2 weeks).

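### The primary model is picked by assumption checks on the trial's own results, and its four-level group-by-time test is not tied to the 12-week focus, so it can be significant without any week-12 benefit

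*Protocol article*

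**What the plan says.** The analysis section of the Protocol article (Statistical methods for primary and secondary outcomes {20a}) makes the model conditional: "If the results of the trial meet the conditions of homogeneity of variance and spherical symmetry", then "the two-factor four-level repeated measurement analysis of variance (group*time) is used; otherwise, the mixed effects model is used". The abstract repeats the rule: "To analyze the data, a two-factor, four-level repeated measures ANOVA will be used if the assumptions of homogeneity of variance and sphericity are met", and "If not, a mixed effects model will be employed".

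The four levels are the four measurements of the primary outcome, VAS pain, "assessed using a visual analog scale at baseline and at 4, 8, and 12 weeks of the post-intervention". Baseline is therefore one of the outcome levels.

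Outcome measures {12} states the time of interest: "We focus on changes in outcomes at 12 weeks after treatment". No section connects this to a term or contrast in the model. Participant timeline {13} places the last visits at "8 weeks of treatment (W9), and 12 weeks of treatment (W13").

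Sample size calculation {14} uses an effect of 0.3, α 0.05, power 0.8, an intraclass correlation of 0.6, two groups and four measurements. It reaches 64, raised to 86 for 25% dropout. It names a two-way repeated measures ANOVA but not the effect being tested.

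**The concern.** Two things are linked here.

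First, the choice between two models rests on features of the outcome data. Which analysis is primary, and which quantity it estimates, is known only once the results are in. The switch is also unnecessary, because a mixed model with unstructured covariance does not need sphericity.

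Second, a four-level group-by-time interaction asks whether the between-group difference varies anywhere across baseline and weeks 4, 8 and 12. The trial's declared question is the change at 12 weeks. A significant interaction could be reported as success when the groups do not differ at week 12. A real week-12 effect could also be tested with less power than the collected data allow.

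**Working it through.** **Inputs.** From Sample size calculation {14}: N = 64 (32 per group), m = 4 measurements, correlation ρ = 0.6, α = 0.05, effect 0.3. Assumptions of this check: compound symmetry; 0.3 read as Cohen's f, which for two groups equals a difference of 2 × 0.3 = 0.6 SD. The protocol gives no SD for the VAS, so effects are in SD units.

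**The plan's own figure.** For the group main effect, λ = f²·N·m/(1 + (m−1)ρ) = 0.09 × 64 × 4/2.8 = 8.23 on 1 and 62 df, giving power 0.806. N = 64 is the smallest even total above 0.80 (62 gives 0.793). Then 64/0.75 = 85.3, so 86. Both figures reproduce. The same f entered for the within-between interaction, λ = f²·N·m/(1−ρ) on 3 and 3(N−2) df, would give N = 14. So 64 belongs to the group main effect.

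That main effect averages over baseline, where randomized groups are expected to be equal. With 0.6 SD at weeks 4, 8 and 12, the averaged difference is 0.45 SD. Its variance factor is 2.8/4 = 0.7, so λ = 16 × 0.45²/0.7 = 4.63 and power is 0.563, not 0.80.

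**The interaction.** λ = (N/4)·SS/(1−ρ) = 16·SS/0.4, where SS is the sum of squared deviations of the four between-group differences from their mean; df 3 and 186.

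| Difference in SD at weeks 0, 4, 8, 12 | SS | λ | Probability of rejection |
|---|---|---|---|
| 0, 0.6, 0, 0 (week 4 only) | 0.27 | 10.8 | 0.787 |
| 0, 0.5, 0, 0 (week 4 only) | 0.1875 | 7.5 | 0.613 |
| 0, 0.6, 0.6, 0 (weeks 4 and 8 only) | 0.36 | 14.4 | 0.898 |
| 0, 0, 0, 0.6 (late) | 0.27 | 10.8 | 0.787 |
| 0, 0.6, 0.6, 0.6 (sustained) | 0.27 | 10.8 | 0.787 |
| 0, 0.2, 0.4, 0.6 (linear build-up) | 0.20 | 8.0 | 0.644 |

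In the first three rows there is no week-12 difference, and a week-12 contrast would reject 5% of the time.

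**Week-12 contrasts for 0.6 SD, same assumptions.**
- Baseline-adjusted: λ = 16 × 0.36/(1 − 0.6²) = 9.0 on 1 and 61 df; power 0.840.
- Unadjusted change from baseline: λ = 16 × 0.36/(2 × 0.4) = 7.2 on 1 and 62 df; power 0.752.
- Week 12 alone: λ = 16 × 0.36 = 5.76 on 1 and 62 df; power 0.656.

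**Sensitivity to the correlation** (interaction against baseline-adjusted contrast, 0.6 SD at week 12).
- ρ = 0.7: 0.898 against 0.911 for a late or sustained effect.
- ρ = 0.8: 0.981 against 0.976 for a late or sustained effect; 0.929 against 0.976 for a linear build-up.
- Serially decaying correlation (AR(1), 0.75, assumed; the switch rule simulated): about 0.81 against 0.74 for a late or sustained effect; 0.42 against 0.73 for a linear build-up.

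**The switch.** A sphericity test followed by model choice was simulated with 8,000 runs per case, a multivariate test standing in for the mixed model. Type I error was 0.057 under compound symmetry and 0.051 under AR(1), with simulation error about 0.0025.

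**The case against.** Several stronger readings are tempting, and the documents do not support them.

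- *The switch makes the primary p-value invalid.* The rule is written in advance and a condition fixes each branch, so the analyst does not choose freely. The simulated error rates show little inflation.
- *The interaction is always the weaker test.* At ρ = 0.6 it beats an unadjusted change contrast for a late or sustained effect (0.787 against 0.752). Against the baseline-adjusted contrast it is level at ρ = 0.8 and ahead under AR(1) for those patterns. Only the linear build-up loses in every case run.
- *The design builds in early differences.* The control drug is "diclofenac diethylamine latex (4 times a day, 7 days per week, for 2 weeks"), and the first visit after baseline is at 4 weeks. No visit falls within the drug period, and nothing says that its effect persists. The week-4-only profile is a hypothetical that shows what the test can do, not a forecast.
- *Baseline as an outcome level is an error.* It is what makes the interaction a comparison of change, so it is legitimate. Adjustment for baseline is the more efficient choice under the planned correlation.
- *The endpoint falls 12 weeks after treatment ends, when controls may have received the trial therapy.* Design {8}, Participant timeline {13} and Table 2 place the last visit at the end of 12 weeks of treatment, and CG Therapy offers the trial therapy only after that. This is loose wording.

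It is also fair that contrasts, covariates and covariance structure are often left to an analysis plan, which is not shown. The missing contrast alone would therefore be a weak point. What stands is positively stated: a switch that depends on results, a four-level group-by-time analysis, a 12-week focus that this analysis does not target, and a sample size that matches a different effect. An analysis plan could name a contrast, but it would have to contradict this text to remove the switch.

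**Conclusion.** The point holds. The primary analysis is not fixed before the results, and the test most naturally read as primary does not answer the 12-week question. Under the planning correlation and compound symmetry, it rejects 79% to 90% of the time for a 0.6 SD difference confined to week 4 or to weeks 4 and 8. For a 0.6 SD week-12 difference it gives up 5 to 20 percentage points of power against a baseline-adjusted contrast (79% to 64%, against 84%); this second result is conditional and should not be stated as a general rule.

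That the interaction is the deciding test is itself a reading, since the text never names the deciding effect. If the group main effect was meant, as the sample size suggests, the test is diluted by baseline and has 56% power for a sustained 0.6 SD difference. Either way, the analysis and sample size sections do not point to the same effect. All figures rest on reading 0.3 as f, that is 0.6 SD. This should be corrected, but the trial's data remain fully usable.

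**What to change.** Remove the assumption-test switch from the analysis section and the abstract. Pre-set one mixed model for repeated measures: VAS at weeks 4, 8 and 12 as outcome; group, visit and group-by-visit; baseline VAS and baseline-by-visit as covariates; unstructured covariance. Name the between-group difference after 12 weeks of treatment (W13), with its 95% CI, as the single primary test. Weeks 4 and 8 and the overall interaction become supportive.

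Restate the power for that contrast, with the effect given as a difference in SD or in mm with an assumed SD. If 0.6 SD is the target, 64 evaluable patients give 84% under the planned correlation and compound symmetry, so the change alone does not force a larger trial. Say how the model fits with the multiple imputation in section {20c}. Use one timing phrase, after 12 weeks of treatment, throughout.

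The cost is a protocol amendment with ethics approval (Protocol amendments {25}) and a more fully specified model. A mixed model is already the fallback, but without these terms. No extra visits, data or software are needed. Recruitment was due to start in July 2023, so the change should be dated and made before any outcome data are examined by group.

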### Eligibility criteria {10]

If a patient expresses interest in participating, researchers will evaluate their eligibility based on the study's inclusion and exclusion criteria (Table 1).

**Table 1 Tab1:** Inclusion and exclusion criteria

Inclusion criteria	Exclusion criteria
18 years old or older	Knee arthroscopy or open surgery in the past 12 months, elective knee replacement
Clinical signs and symptoms corresponding to KOA, according to the 2021 COA guidelines	With other joint problems (such as severe osteoporosis, rheumatoid arthritis, fracture, gout, joint tuberculosis, or joint tumor)
Kellgren-Lawrence Grade I–III of KOA	Malignant illness or other major conditions (e.g., unstable cardiovascular disorders or lung disease, dementia) that restrict the ability to adhere to the recommended treatment
Visual analog scale (VAS) score ≥ 4 points [19]	Cognitive impairment resulting in the inability to understand the physical therapist’s instructions and the content in the app
Access to smartphone or tablet	Pregnant women
Participate in the experiment voluntarily and sign the informed consent	The supervision and care of other family members cannot be guaranteed for each exercise training
Accept randomization assignment	Neurological disorders
Candidates who meet all the above criteria will be included	Candidates meeting any of the above criteria will be excluded

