#### Primary outcome measure

##### Pain intensity

A visual analog scale (VAS) is used to evaluate knee pain. Patients will be asked to rate their current pain level on a line of 100 mm in length, with 0 representing no pain and 100 representing extreme pain, and patients mark this point on the current pain line. The VAS score is then determined by measuring in millimeters from the left end of the line to the point marked by the patient. Patients can experience pain ranging from no pain to extreme pain. Scores range from 0 to 100, with higher scores indicating more severe pain [26].

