#### Methods in analysis to handle protocol non-adherence and any statistical methods to handle missing data {20c}

We will evaluate the loss of primary outcome data through intention-to-treat analysis. Missing data will be reduced to a minimum by using the multiple imputation.

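### The 18 mm responder comparison ignores baseline VAS: a valid test, but less efficient and more exposed to chance baseline imbalance than it needs to be

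*Protocol article*

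**What the plan says.** All places are in the protocol article.

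- **Responder test** (Statistical methods, item 20a): "A chi-square test will be used to infer the proportion of the number of patients meeting the MCID between the two groups". No covariate or stratification is attached to it.
- **Threshold** (same section): the MCID is reached when VAS pain "is changed by 18 mm based on 100 mm". The sentence describes this as a change between the two groups, yet the test counts individual patients.
- **Scale** (Pain intensity): "Scores range from 0 to 100, with higher scores indicating more severe pain".
- **Entry** (Table 1): a VAS of at least 4 points, which on the 100 mm line I read as at least 40 mm. That reading is an assumption.
- **Time point** (Outcome measures, item 12): "We focus on changes in outcomes at 12 weeks after treatment". The responder sentence names no visit.
- **Main analysis** (item 20a): "the two-factor four-level repeated measurement analysis of variance (group*time) is used; otherwise, the mixed effects model is used", with "2-sided *P* < 0.05 considered to be statistically significant".
- **Missing data** (item 20c): "Missing data will be reduced to a minimum by using the multiple imputation".
- **Randomisation** (items 16a to 16c): permuted blocks of 4. No stratification by pain is mentioned.
- **Use of baseline pain** (item 20a): it is compared between groups. No adjustment for it is named for the responder test.

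**The concern.** A responder is defined by a fixed drop on a bounded scale, in patients selected for having pain at entry. Someone who starts at 80 mm has more room to fall, and more regression to the mean, than someone who starts at 42 mm. Baseline VAS therefore predicts responder status even without any treatment effect.

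Two things follow when it is left out. Variation that could be explained stays in the comparison, which costs power. And if one arm happens to start with more pain, that arm collects more responders for that reason alone. A between-group test of baseline pain would show such an imbalance but not correct it. Adjustment decided after seeing it would look data-driven.

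The responder proportion is the plan's patient-level reading of clinical importance, so readers are likely to quote it.

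**Working it through.** **1. The plan's own sample size.** Inputs from item 14: effect 0.3 (it reproduces only as Cohen's f), alpha 0.05, power 0.8, correlation 0.6, two groups, four measurements. For the between-groups test of a repeated measures ANOVA, lambda = f² × N × m / (1 + (m − 1) × rho).

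- N = 64: 0.09 × 64 × 4 / (1 + 3 × 0.6) = 23.04 / 2.8 = 8.23, power 80.6%. N = 62 gives 79.3%.
- Dropout: 64 / 0.75 = 85.3, rounded up to 86.

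Both figures reproduce. They concern the ANOVA. No power or responder rate is stated for the MCID comparison.

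**2. Assumptions needed beyond the documents.** Baseline normal with mean 60 and SD 20 mm, truncated to 40–100 mm (resulting SD about 14.3 mm); correlation with the 12-week value 0.3, 0.6 or 0.8; mean shift of 10 mm in controls; treatment effect 0 or 12 mm. A fourth model uses a proportional response, with a 20% drop in controls. There were 10,000 simulated trials per scenario. The Pearson chi-square on a drop of at least 18 mm was compared with a likelihood-ratio logistic test adjusted for baseline.

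**3. Does baseline predict response?** With no treatment effect, 17% to 29% respond when baseline is below 50 mm, and 37% to 63% when it is 70 mm or more.

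**4. Chance imbalance.** The SD of the difference in mean baseline is 14.3 × √(2/43) = 3.1 mm at N = 86 and 14.3 × √(2/32) = 3.6 mm at N = 64. Each mm moves the responder difference by about 0.5 to 1.3 percentage points, so a 1-SD imbalance moves it by about 1.5 to 4.8 points. At N = 86, correlation 0.6 and a true difference of about 27 points, the mean estimate is 32 points when the trial arm starts more than 5 mm higher and 22 when it starts more than 5 mm lower.

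**5. Power for a 12 mm effect, chi-square → baseline-adjusted.**

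| Scenario | N = 86 | N = 64 |
|---|---|---|
| Correlation 0.3 | 52% → 61% | 45% → 48% |
| Correlation 0.6 | 72% → 76% | 63% → 64% |
| Correlation 0.8 | 94% → 95% | 88% → 88% |
| Proportional response | 80% → 82% | 71% → 71% |

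A smaller simulation (1,500 trials per scenario, 43 per arm) gave 73% → 78% (SD 20, correlation 0.6), 60% → 66% (SD 20, correlation 0.4) and 55% → 59% (SD 25, correlation 0.6).

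**6. The 9-point gain is partly an artefact of whole-number counts.** In that scenario the pooled responder rate is about (0.41 + 0.63)/2 = 0.52.

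- 43 per arm: a difference of 9 patients gives z = (9/43) / √(2 × 0.52 × 0.48/43) = 1.94, just short of 1.96. Ten patients are needed, at z = 2.16.
- 32 per arm: 8 patients give z = (8/32) / √(2 × 0.52 × 0.48/32) = 2.00, just enough.

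The chi-square is thus unluckily strict at 43 per arm, and part of its deficit there has nothing to do with baseline.

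**7. Type I error.** It is 5.2% to 5.8% for the chi-square and 5.2% to 5.8% for the adjusted test. In the smaller simulation the ranges were 5% to 6% and 5% to 6.6%.

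**The case against.** The strongest reply is that nothing here is invalid, and that stands. Under 1:1 randomisation the chi-square is unbiased on average and holds its error rate. With about 35% responders and 43 per arm, the standard error of the difference is √(2 × 0.35 × 0.65/43), about 10 percentage points. The shift from a 1-SD baseline imbalance is less than half of that and is already part of the chance variation that the p-value allows for. The analysis is also supportive, because the main one is the repeated measures ANOVA or mixed model. Dichotomising costs more than omitting baseline: in a separate run of 2,000 trials at correlation 0.6 and N = 86, ANCOVA on the VAS itself had about 92% power, against about 70% for the chi-square.

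A reader might also infer three stronger things that the documents do not support:

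- **That no effect size will accompany the test.** Item 20a promises effect sizes for all outcome indicators. It names no interval, but an article may leave that out.
- **That the chi-square cannot be combined with multiple imputation.** The statistic itself is not an estimate with a standard error, but the same unadjusted comparison can be pooled as a risk difference, and methods for pooling chi-square statistics exist. The choice is ordinary analysis-plan detail.
- **That this is the only judgement of clinical relevance.** Item 20a also judges effect sizes by Cohen's criteria to reach conclusions.

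What survives is that the protocol names a specific test without the one covariate that is built into the outcome's definition and already measured.

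**Conclusion.** The point holds as a minor gain in precision for a supportive analysis. It is not a validity error, and nothing suggests that the planned test would mislead on average.

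Under the stated assumptions, the responder difference moves about 0.5 to 1.3 percentage points per mm of baseline imbalance. Adjustment adds about 0 to 9 points of power if all 86 patients contribute and 0 to 3 if 64 do. The upper end depends on a low correlation and partly on the whole-number effect at 43 per arm; with a correlation of 0.8 or a proportional response the gain is 0 to 2 points. All these figures rest on an assumed SD, correlation, treatment effect and 40 mm entry floor. That responder status depends on baseline held in every scenario tried.

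The wording of the responder definition needs settling in any case. A change between groups is not something that an individual patient can meet.

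**What to change.** In item 20a:

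1. Define a responder as a patient whose VAS falls by at least 18 mm from that patient's own baseline at the 12-week visit. This replaces the between-group wording and ties the outcome to the time point named in item 12.
2. Replace the chi-square with a logistic regression of responder status on group and continuous baseline VAS, fitted in each imputed dataset and pooled by Rubin's rules.
3. Report the pooled adjusted odds ratio with a 95% confidence interval, the responder proportion in each group and, if wanted, a standardised risk difference.

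No extra patient, visit or measurement is needed, and SPSS fits the model. The cost is slightly more analysis work. A standardised risk difference needs one further step, because logistic regression yields a conditional odds ratio rather than a difference in proportions, and that step must also be pooled over the imputations.
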